### Aim 2: Assess Using Temporal Features’ Impact on Risk Warning Timeliness

The discussion below is for IH data. The cases with KPSC and UWM data and with asthma are similar.

#### Outcome of the Number of Days of Early Warning the Model Provides for the Patient and the Estimation Approach

Consider a predictive model and a patient who used the hospital on date *D* in the 14th year. The outcome is the number of days of early warning the model provides for the patient. To measure the number, we find the first date *D'* (*D*-365≤ *D'* ≤ *D*-1) such that if we use *D'* as the prediction time point and input the patient’s history up to *D'* into the model, the model predicts hospital use in the subsequent year. In this case, the model warns the first hospital use *k* (0≤ *k* ≤ *D-D'*) days in advance, with *D'* + *k* being the first day between *D'* and *D* when the patient used the hospital. *k* is the outcome number. Otherwise, if the model still predicts no hospital use when we reach *D*-1, the model warns zero day in advance and zero is the outcome number. We expect using our techniques will raise the outcome number. We will assess the outcome on the cohort of COPD patients who ever used the hospital during the 14th year. For these patients, the average number of days of early warning given by the model shows how timely it warns.

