### Datasets

We will employ clinical and administrative data from the enterprise data warehouses (EDWs) of 3 leading health care systems: Intermountain Healthcare (IH), Kaiser Permanente Southern California (KPSC), and UWM, as well as publicly available air quality and weather data. All of the data to be used are structured. We will use all patients’ data that are needed for computing health care system features [64,65], rather than only COPD and asthma patients’ data. As the largest health care system in Utah, IH has 185 clinics and 22 hospitals. The EDW of IH contains numerous variables [66]. In this study, we will start with using the following of these variables: “admission date and time; age; orders (medications, labs, exams, immunizations, imaging, and counseling), including order name, ordering provider, performing date, and result date; allergies; barriers (hearing, language, learning disability, mental status, religion, and vision); cause of death; chief complaint; death date; diagnoses; discharge date; exam result; facility seen for the patient visit; gender; health insurance; healthcare cost; height; home address; immunizations; lab test result; languages spoken; medication refills; primary care physician as listed in the electronic medical record; problem list; procedure date; procedures; provider involved in the visit; race/ethnicity; referrals; religion; visit type (inpatient, outpatient, urgent care, or emergency department); vital signs; weight” [65]. An IH data analyst will download a de-identified IH dataset, encrypt it, and transfer it to the secure computer cluster. The IH dataset has information on clinical encounters in the previous 14 years (2005 to 2018). For the previous 5 years, the IH data for adults cover over 5,786,414 clinical encounters and 878,448 adult patients (aged ≥18 years) per year. The IH data for children cover over 1,557,713 clinical encounters and 360,698 pediatric patients (aged <18 years) per year. COPD prevalence is approximately 4.1% in the IH adult population. Asthma prevalence is approximately 8.6% and 7.6% in the IH adult and pediatric population, respectively. The IH dataset provides the electronic record of care for approximately 60% of adults and approximately 95% of children in Utah [56,67]. IH devotes many resources to maintain data integrity and accuracy. Owing to its huge size and variable richness, the dataset provides many advantages for us to explore the proposed predictive models.

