#### Chronic Obstructive Pulmonary Disease and Asthma Cases and Outcomes

As test cases, we will develop and test our approach using (1) COPD, (2) pediatric asthma, and (3) adult asthma. For COPD, we will adjust the criteria used by the Centers for Medicare and Medicaid Services and National Quality Forum [78-80] to incorporate outpatient and emergency room visit data [81] to find COPD patients. A patient is deemed to have COPD if he/she is ≥40 years and has one of the following:

1 outpatient visit diagnosis code of COPD (International Classification of Diseases, Ninth Revision [ICD-9]: 491.21, 491.22, 491.8, 491.9, 492.8, 493.20, 493.21, 493.22, 496; International Classification of Diseases, Tenth Revision [ICD-10]: J41.8, J42, J43.*, J44.*) and ≥1 prescription of tiotropium within 6 months of the outpatient visit.≥2 outpatient or ≥1 emergency room visit diagnosis codes of COPD (ICD-9: 491.21, 491.22, 491.8, 491.9, 492.8, 493.20, 493.21, 493.22, 496; ICD-10: J41.8, J42, J43.*, J44.*).≥1 hospital primary discharge diagnosis code of COPD (ICD-9: 491.21, 491.22, 491.8, 491.9, 492.8, 493.20, 493.21, 493.22, 496; ICD-10: J41.8, J42, J43.*, J44.*).≥1 hospitalization with a primary discharge diagnosis code of respiratory failure (ICD-9: 518.81, 518.82, 518.84, 799.1; ICD-10: J80, J96.0*, J96.2*, J96.9*, R09.2) and a secondary discharge diagnosis code of acute exacerbation of COPD (ICD-9: 491.21, 491.22, 493.21, 493.22; ICD-10: J44.0, J44.1).

The outcome measure is whether a patient used the hospital (inpatient stay and emergency room visit) with a primary diagnosis of COPD (ICD-9: 491.21, 491.22, 491.8, 491.9, 492.8, 493.20, 493.21, 493.22, 496; ICD-10: J41.8, J42, J43.*, J44.*) in the subsequent year.

For asthma, we will use Schatz et al’s [20,82,83] method to find asthma patients. A patient is deemed to “have asthma if he/she has 1) ≥1 diagnosis code of asthma (ICD-9 493.*; ICD-10 J45/J46.*) or 2) ≥2 asthma-related medication dispensing records (excluding oral steroids) in a one-year period, including β-agonists (excluding oral terbutaline), inhaled steroids, other inhaled anti-inflammatory drugs, and oral leukotriene modifiers.” [84] The outcome measure is whether a patient used the hospital with a primary diagnosis of asthma (ICD-9 493.*; ICD-10 J45/J46.*) in the subsequent year.

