#### Accuracy Evaluation and Justification of the Sample Size

The discussion below is for IH data. The cases with KPSC and UWM data are similar. As we need to compute outcomes for the subsequent year, we essentially possess 13 years of IH data over the past 14 years. We will train and test models in a usual way. We will do a stratified 10-fold cross-validation [61] on the data in the first 12 years to train models and to estimate their accuracy. The data in the 13th year will be employed to gauge the performance of the best models, mirroring future use in clinical practice. We will select the best model using the standard performance metric AUC [61]. A care management program typically enrolls 1% to 3% of COPD patients [32]. Of the upper 1% of COPD patients the model projects to be at the highest risk of using the hospital, we will report the percentage of patients using the hospital in the subsequent year. For a program taking 1% of COPD patients based on the model’s prediction results, this percentage reflects the degree of correct enrollment. To find the variables vital for high accuracy, we will conduct backward elimination [74] to remove features on the condition that accuracy does not drop >0.02. We will compare the variables vital for high accuracy on IH data with those on KPSC and UWM data. Using the variables available in both the IH and KPSC/UWM datasets, we will build the best predictive model on IH data and compare the model’s accuracy on IH data with that on KPSC/UWM data.

We will test the hypothesis that using our techniques can boost model accuracy. To do this, we will use a 2-sided Z test to compare the AUCs of 2 predictive models built in a way like that in Obuchowski [101]. The first predictive model will use the best machine learning algorithm and take all features essential for high accuracy. The second model will be adapted from those in the literature. For each predictive model for hospital usage reported in the literature [19-28], we will retrain it on our dataset using the attributes appearing in both the original model and our dataset. The most accurate one of the retrained models will be the second model. Our hypothesis is as follows:

Null hypothesis: The first model reaches the same AUC as the second.Alternative hypothesis: The first model reaches a higher AUC than the second.

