#### Outcome Evaluation and Justification of the Sample Size

We will test the hypothesis that using our techniques can boost risk warning timeliness. To do this, for the patient cohort, we will use an *F* test to compare the number of days of early warnings provided by the 2 models mentioned in Aim 1’s accuracy evaluation section, assuming a Poisson model with an offset of 365 days. Our hypothesis is as follows:

Null hypothesis: The number of days of early warning provided by the first model is the same as that provided by the second.Alternative hypothesis: The number of days of early warning provided by the first model is larger than that provided by the second.

Assuming the number of days of early warning has an exponential distribution and employing an *F* test at a one-sided significance level of 0.05, a sample size of 600 patients offers 80% power to detect a minimum raise of 27.8 days of early warning by the first model, when the second model warns, on average, 180 days in advance. About 2000 COPD patients ever used IH hospitals during the 14th year, giving enough power to test our hypothesis. The conclusion remains valid if the actual situation differs somewhat from the assumed one.

For Aims 1 and 2, our goal is to reach a boost of ≥0.1 in accuracy and ≥30 days in risk warning timeliness, respectively. If we cannot reach this goal on the entire COPD patient group, we will construct distinct models for differing patient subgroups. The patient subgroups are described by characteristics such as age or co-morbidity, which are often independent variables in the original predictive models. If we still cannot reach this goal, we will do subanalyses to find the patient subgroups, for which our predictive models show good performance, and then apply our ultimate predictive models only to these patient subgroups.

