#### Procedures

From the IH data in the 13th year, we will randomly select 400 IH COPD patients who used the hospital in the subsequent year and automatically explain the prediction results of the best IH model built in Aim 4. We will use patients outside of UWM to help ensure no care manager is aware of any of those patients’ outcome in the subsequent year. We will show every care manager a different subset of 40 patients and proceed in 3 steps:

Step 1: For every patient, we will present the historical de-identified patient attributes and the prediction result to the care manager and ask him/her to record the enrollment decision and interventions, if any, that he/she plans to use on the patient. For the historical patient attributes, we will show the static attributes’ values at the top, followed by the longitudinal attributes’ values in reverse chronological order. No care manager will see any automatic explanation in this step.Step 2: For every patient, we will present the automatic explanations and their linked interventions to the care manager and survey him/her using both semistructured and open-ended questions. The automatic explanations will appear as a list of association rules. Below each rule is the list of interventions linked to the rule. The questions will include whether these explanations would change the enrollment decision for the patient, whether he/she believes they would improve care plan quality, their usefulness on a 1 to 7 scale with anchors of not at all/very useful, and their perceived trustworthiness on a 1 to 7 scale with anchors of not at all/completely. Our questionnaire will embrace a text field for writing comments.Step 3: We will use the standard Technology Acceptance Model (TAM) satisfaction questionnaire [107] to survey the care manager about the automatic explanations. A technology is unimportant unless people will accept and use it. Developed based on multiple well-accepted behavioral theories, TAM is the most widely adopted model of people’s acceptance and usage of a technology. The TAM satisfaction questionnaire will measure the perceived usefulness and the perceived ease of use of automatic explanations. Perceived usefulness is known to link strongly to future usage intentions and to actual function usage [108,109]. Multiple studies have demonstrated the validity and reliability of the TAM satisfaction questionnaire [110,111].

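### Aim 2 measures early-warning days partly with look-ahead: the Aim 1 models it reuses are trained on labels through year 13, and every scan starts in year 13

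*Protocol article*

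**What the plan says.** All places are in the protocol article.

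- **Datasets:** the IH data hold "clinical encounters in the previous 14 years (2005 to 2018"), so year 13 is 2017 and year 14 is 2018.
- **Chronic Obstructive Pulmonary Disease and Asthma Cases and Outcomes:** "The outcome measure is whether a patient used the hospital (inpatient stay and emergency room visit) with a primary diagnosis of COPD" in the year that follows.
- **Aim 1, Accuracy Evaluation and Justification of the Sample Size:** "As we need to compute outcomes for the subsequent year, we essentially possess 13 years of IH data over the past 14 years". Then: "We will do a stratified 10-fold cross-validation [61] on the data in the first 12 years to train models and to estimate their accuracy", and "The data in the 13th year will be employed to gauge the performance of the best models".
- **Aim 1's Final Predictive Models:** at each system the models are built on all of its COPD patients. No split by patient is stated.
- **Aim 2, definition of the outcome:** "Consider a predictive model and a patient who used the hospital on date" D in year 14. Candidate dates D' run from D-365 to D-1. The first D' with a positive prediction counts. The number of days, k, runs from D' to the first hospital use between D' and D. The cohort is all COPD patients with hospital use in year 14.
- **Aim 2, Outcome Evaluation:** an F test will "compare the number of days of early warnings provided by the 2 models mentioned in Aim 1". No retraining with an earlier cut-off is mentioned.

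**The concern.** In Aim 1 a data year is an index year whose label lies in the next year. Training on years 1 to 12 therefore uses hospital use in year 13 as the label of the year-12 instances. The Aim 1 test respects time order, since it uses index year 13 with the label in year 14. Aim 2 takes the same fitted models and moves the prediction date back by up to a year, into the period that supplied the last training labels, for patients who may themselves be in the training set.

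A model scoring a patient early in year 13 could not, in real use, have been trained on outcomes up to the end of year 13. Aim 1 sets resemblance to future clinical use as the purpose of its held-out year, and Aim 2 loses that resemblance. Because the endpoint is the first positive date, the part of the window with the most overlap is searched first. At stake are the one-sided test of warning days and the goal of a gain of at least 30 days.

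**Working it through.** **The plan's own figure.** Inputs from Aim 2, Outcome Evaluation: 600 patients, mean 180 days, raise 27.8 days, one-sided 0.05, exponential distribution. The ratio of means is 207.8/180 = 1.1544. With 600 values per model treated as independent, power = P(F(1200,1200) > F_crit/1.1544) = 0.8001. The normal approximation n = 2 × ((1.645 + 0.842)/ln 1.1544)² gives 599.5. The stated 600 patients and 80% power reproduce. The point here concerns what is measured, not this calculation.

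**Step 1: label period.** Fourteen calendar years give 13 index years. Training index years 1 to 12 carry labels in years 2 to 13. The test index year 13 carries its label in year 14. Aim 5, Experiment 1 uses the same convention: "From the IH data in the 13th year, we will randomly select 400 IH COPD patients who used the hospital in the subsequent year".

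**Step 2: scan start.** Let D be day d of year 14 (d = 1 to 365). Then D-365 is day d of year 13. All 365 possible scans start in year 13.

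**Step 3: share of scan dates in year 13.** For a given d, 366 - d of the 365 scan dates lie in year 13. With D uniform over the year, the share is (365 × 366/2)/365² = 366/730 = 50.1%.

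**Step 4: overlap of the predicted window with the label period.** A prediction on day e of year 13 covers the next 365 days, of which 365 - e lie in year 13. A prediction in year 14 has no overlap.

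- First scan date (e = d): the mean of 365 - d is 182 days (range 0 to 364), and 182/365 = 49.9%. The overlap is at least 90% only for d ≤ 36, that is 36/365 = 9.9% of possible D.
- All scan dates: the summed overlap is the sum over d of (365 - d)(366 - d)/2 = 364 × 365 × 366/6. Divided by 365³ this is 16.7%.
- Scan dates with at least half their window in the label period (e ≤ 182): (182 × 183/2)/365² = 12.5%.

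**Step 5: other sites.** The article says KPSC and UWM are handled similarly. KPSC (2009 to 2018) then trains on index years 2009 to 2016, and UWM (2012 to 2018) on 2012 to 2016. Labels run through 2017 at both, so the same overlap arises.

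**Step 6: direction.** A patient with year-13 use has a positive last training label, which favours an early warning. A patient whose only use is in year 14 has a negative one, which works against it. For the first group k stops at the first use after D', which may itself be the year-13 event, and this limits any inflation. The article gives no split between these groups.

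**The case against.** The strongest counter-case has four parts.

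**The overlap is partial.** A reader might infer from the 50% in step 3 that half of the measurement is in-sample. It is not. That figure counts scan dates. The predicted outcome overlaps the label period by about one sixth on average. Use in year 14 is never a training label, dates in year 14 are clean, and patients first identified as having COPD after year 12 have no training instance. This stands.

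**Scored rows are not training rows.** A reader might infer that a flexible model simply recalls its labels and so inflates the first model's warning days. The inputs at D' include history from year 13, so they nearly match the year-12 instance only when D falls very early in year 14. Simulation results depend almost wholly on this. In one illustrative set-up with assumed data, a fully grown forest had sensitivity 0.74 with the label in training v 0.18 without it on the exact training row. With features half moved on this became 0.25 v 0.13, and with a minimum leaf of 100 it became 0.20 v 0.17. None of these figures estimates the bias here, because the article does not fix the final algorithm. Both models are also retrained on the same data, so only a difference in fit biases the comparison. This stands.

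**The wording may allow a cut-off.** Aim 1 says models are built with history up to the prediction time point, and the article defers detail to a design paper that is not shown. But Aim 2 names the two Aim 1 models, and Aim 1 fixes their training years. The wording does not undo the overlap.

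**The repair is not one training run.** Temporal features are learned from the training data and then defined by people, and algorithm selection uses the same data. This stands and enters the cost.

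**Conclusion.** The look-ahead is real and follows from what the article fixes: training years, models, scan window and cohort. Every scan starts inside the last training-label year, with overlap of about 50% at the first scan date and about 17% over all scan dates. These figures assume D uniform over year 14 and the index-year reading, which the article uses consistently but does not spell out for year-13 labels.

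The test of warning days is biased to the extent that the two models fit their training labels differently. This is plausible, because the first model comes from an automated search over algorithms and features while the second is a retrained literature model. It cannot be shown from the article. Neither the size nor the net direction can be stated, and a claim that the first model's gain is inflated would go beyond the documents. The Aim 1 accuracy test is unaffected. The design should be corrected before analysis, since an earlier label cut-off removes the problem whatever its size.

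**What to change.** For Aim 2 only, build both models on index years 1 to 11, so that labels end in year 12 and every scan date falls after the last label. Include the data-driven feature extraction and the model selection in this refit. At minimum, refit the final models with that cut-off and disclose that the feature definitions came from years 1 to 12. Apply the same one-year gap at KPSC and UWM, and for asthma.

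This keeps the 365-day scan, the cohort of about 2000 and the power figure. Restricting D' to year 14 would also remove the overlap, but it caps k at 182 days on average, which does not fit a planning mean of 180 days.

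The cost is a second pass of the model-building pipeline and one fewer training year: 12 to 11 at IH, 8 to 7 at KPSC, and 5 to 4 at UWM, where the loss is one fifth. The Aim 2 models would then be refits of the Aim 1 models, not the same models, and the report should say so.

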#### Outcome Evaluation and Justification of the Sample Size

We will test the hypothesis that using our techniques can boost risk warning timeliness. To do this, for the patient cohort, we will use an *F* test to compare the number of days of early warnings provided by the 2 models mentioned in Aim 1’s accuracy evaluation section, assuming a Poisson model with an offset of 365 days. Our hypothesis is as follows:

Null hypothesis: The number of days of early warning provided by the first model is the same as that provided by the second.Alternative hypothesis: The number of days of early warning provided by the first model is larger than that provided by the second.

Assuming the number of days of early warning has an exponential distribution and employing an *F* test at a one-sided significance level of 0.05, a sample size of 600 patients offers 80% power to detect a minimum raise of 27.8 days of early warning by the first model, when the second model warns, on average, 180 days in advance. About 2000 COPD patients ever used IH hospitals during the 14th year, giving enough power to test our hypothesis. The conclusion remains valid if the actual situation differs somewhat from the assumed one.

For Aims 1 and 2, our goal is to reach a boost of ≥0.1 in accuracy and ≥30 days in risk warning timeliness, respectively. If we cannot reach this goal on the entire COPD patient group, we will construct distinct models for differing patient subgroups. The patient subgroups are described by characteristics such as age or co-morbidity, which are often independent variables in the original predictive models. If we still cannot reach this goal, we will do subanalyses to find the patient subgroups, for which our predictive models show good performance, and then apply our ultimate predictive models only to these patient subgroups.

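### Aim 2 tests days of early warning under a Poisson model but sizes the test under an exponential one, and neither step states how the pairing of the two models within patient is handled

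*Protocol article*

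**What the plan says.** In the Protocol article, Aim 2, the section defining the outcome gives each patient one number per model. It is the number of days between the model's first warning and the first hospital use after that warning. The search starts at most 365 days before the index hospital use, so the number cannot exceed 365. If no warning comes, "the model warns zero day in advance and zero is the outcome number". The cohort is the COPD patients who used the hospital in year 14.

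The next section, Outcome Evaluation and Justification of the Sample Size, uses an F test "to compare the number of days of early warnings provided by the 2 models mentioned in Aim 1’s accuracy evaluation section", on this one cohort and "assuming a Poisson model with an offset of 365 days". It names no patient effect, within-patient difference or dispersion parameter.

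The sizing paragraph then changes distribution: "Assuming the number of days of early warning has an exponential distribution". It states that "a sample size of 600 patients offers 80% power to detect a minimum raise of 27.8 days" (one-sided 0.05), "when the second model warns, on average, 180 days in advance". About 2000 such patients are available at IH.

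Elsewhere the article does allow for dependence. Aim 1 assumes a correlation of 0.6 between the two models' predictions, Aim 3 applies McNemar's test to the same two models as paired samples, and Aim 5 uses random effects.

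**The concern.** Two distributions are assigned to one outcome within one section, and they imply very different standard errors. The Poisson model fixes the variance at the mean; the exponential sets the standard deviation equal to the mean. A test whose variance comes from the first assumption while the data look like the second would understate its standard error severely.

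Each patient also contributes two values. Two models reading the same record will very probably agree to some degree, and a comparison that treats the values as independent uses the wrong variance for the difference.

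This is the only hypothesis test for Aim 2, and the article extends it to KPSC, UWM and asthma. At stake is whether its P value for earlier warning can be taken at face value.

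**Working it through.** **Inputs from the article.** One-sided alpha 0.05; 600 patients; 80% power; means 180 and 180 + 27.8 = 207.8 days; exponential for sizing; Poisson for analysis; outcome range 0-365; about 2000 patients at IH. The within-patient correlation and the true shape of the outcome are not given and are assumed below.

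**1. Reproducing the plan's figure.** For two independent exponential samples of n each, the ratio of sample means is the true ratio times an F variable with (2n, 2n) degrees of freedom. The true ratio is 207.8/180 = 1.1544.
- 600 v 600, one-sided 0.05: power 0.800, detectable raise 27.80 days. This matches.
- 300 v 300, one-sided: power 0.545.
- 600 v 600, two-sided: power 0.701.
- Log-ratio check: n = 2 × [(1.645 + 0.842)/ln(1.1544)]² = 2 × (2.487/0.1436)² ≈ 599.5 per sample.

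The arithmetic is right, but it takes 600 patients as two independent samples of 600, that is, zero within-patient correlation.

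**2. The two distributions at mean 180.**
- Poisson: variance 180, SD √180 = 13.4 days.
- Exponential: variance 180² = 32,400, SD 180 days.
- Variance ratio 32,400/180 = 180; standard-error ratio √180 = 13.4.

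**3. Fit to a 0-365 outcome.** An exponential puts exp(−365/180) = 13.2% of values above 365 at mean 180, and exp(−365/207.8) = 17.3% at mean 207.8. Neither distribution imposes the upper bound or describes patients set to 0 because they were never warned.

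**4. Type I error, nominal one-sided 0.05, no true difference.** Assumptions: 600 patients, 2,000 runs, four shapes (exponential, exponential capped at 365, and two bounded shapes, one of them U-shaped), means set at 180 before any capping, latent correlation 0, 0.5 or 0.8. Ranges are over the four shapes.

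| Test | corr. 0 | corr. 0.5 | corr. 0.8 |
|---|---|---|---|
| Poisson, dispersion 1 | 0.404-0.448 | 0.376-0.438 | 0.324-0.402 |
| Dispersion-scaled F, no pairing | 0.052-0.055 | 0.012-0.019 | 0.000-0.002 |
| Exponential F, no pairing | 0.004-0.052 | 0.000-0.012 | 0.000 |
| Paired t | 0.050-0.054 | 0.042-0.050 | 0.044-0.059 |

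With 2,000 patients, 3,000 runs and two bounded shapes, the results were 0.37-0.45 for Poisson with dispersion 1; for the scaled test without pairing, 0.010-0.015 at correlation 0.5 and 0.001-0.002 at 0.8; and about 0.04-0.06 for the paired test.

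**5. Power without pairing at 2000 patients.** Exponential, zero correlation: SE of the log ratio = √(2/2000) = 0.0316; 0.1436/0.0316 = 4.54; 4.54 − 1.645 = 2.90, so power is about 0.998. In the simulations of 2,000 patients, the scaled test without pairing had power of at least 0.98 for every shape and correlation.

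**6. Detectable difference under pairing, 600 patients.** With SDs of 180 and 207.8, SD² of the difference = 180² + 207.8² − 2ρ(180)(207.8) = 75,581 − 74,808ρ. Detectable difference = 2.487 × SD/√600.
- ρ = 0: SD 274.9, 27.9 days
- ρ = 0.3: SD 230.5, 23.4 days
- ρ = 0.5: SD 195.4, 19.8 days
- ρ = 0.8: SD 125.4, 12.7 days

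On the log-ratio scale, the pairs needed for the plan's 27.8 days are 599.5 × (1 − ρ): about 599, 420, 300 and 120.

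**The case against.** The article never says that the values are treated as independent, nor that dispersion is fixed at 1. It is a condensed report, and a patient term or a dispersion estimate could sit in a fuller plan. Naming an F test favours the milder reading, since in Poisson regression an F test ordinarily goes with an estimated dispersion and a fixed dispersion with a chi-square or z test. On that reading type I error is not inflated. The test is at level with zero correlation and conservative with positive correlation, and the available cohort leaves ample power. Sizing as if independent is then a safe upper bound.

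The stated target of at least 30 days is a further guard. With SD 180 and 2000 uncorrelated pairs, the SE of the difference is 180 × √(2/2000) = 5.7 days, so a chance gain of 30 days lies more than 5 SEs out.

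Most of this stands. A reader might infer that Aim 2 has a false-positive rate near 40%, or that the cohort is too small. The article supports neither: the first needs dispersion fixed at 1, which is not stated, and the sample-size arithmetic is correct. Nor is the constant 365-day offset a fault. It cancels from the comparison and is harmless, although it does not impose the bound.

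What the objection does not remove is the conflict between two stated distributions. A fuller plan could add detail, but it cannot make both true of one outcome. The article's allowance for its assumptions being somewhat off does not stretch to a 180-fold difference in variance.

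**Conclusion.** The point holds as an inconsistency in the stated analysis. The testing and sizing distributions contradict each other, neither fits the bounded outcome, and pairing appears to be left out of both steps. That last part is an inference from the missing patient term and from the reproduction as two independent samples; Aim 3's paired treatment of the same two models makes the omission harder to explain.

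The consequence depends on a choice that the article does not state. With dispersion fixed at 1, one-sided type I error is about 0.37-0.45. With estimated dispersion it is about 0.05 at zero correlation and about 0.001-0.015 at 0.5-0.8, at little cost in power. These figures rest on assumed shapes and correlations, and the statement about ample power concerns IH, the only system for which Aim 2 gives a cohort size. Severity: should-fix. The number of patients is not in question.

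**What to change.** State one within-patient analysis and use it for both the test and the sizing. Suitable choices are the mean paired difference in days with a patient-level bootstrap or paired t confidence interval, or a model clustered by patient with robust variance. Drop the Poisson and exponential assumptions, or keep one only as a working model under robust variance.

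Restate the detectable difference from an assumed SD of the paired difference over a range of correlations, as in step 6. At zero correlation it stays near 600 patients and 27.8 days, and it improves as correlation rises. Apply the same wording to KPSC, UWM and asthma.

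The cost is a changed analysis sentence and a recalculated sizing sentence. No new data are needed, and by the article's own timetable data analysis had not begun.
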